#### Feedback

The teaching of correct iER strategies is mainly achieved by varying feedback. Ultimately, the player cannot proceed and finish the game when using the wrong (i.e. maladaptive) strategies. Specifically, there will be:
Audio and visual feedback: sounds and pictures (similar to emojis, e.g. heart-shaped) over the receiving agent’s head will indicate if a strategy was successful.Feedback from receiving agents: Receiving agents will clarify if a strategy was good (e.g. “Thank you for listening to me without interrupting!”) or maladaptive in this situation (e.g. “That just made me feel worse.”).Rewards and achievements: After some successful interactions, the player gets rewarded with items (received as gifts from the receiving agent). Items can be sold for in-game money or are needed in further interactions or levels to proceed in the game.

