*Sex differences*. Sex differences will be examined in the experimental subgroup of our sample. During gameplay, the player undergoes 10 different scenarios, where they interact with NPCs by choosing one of up to four dialogue options. The four different strategies according to Niven, Totterdell [4] will be presented during these interactions. The dialogue options will consist of two adaptive and two maladaptive strategies (on average, with a range of 2–4 adaptive options, but always including both strategies of “positive engagement” and “acceptance”). Each picked option will be saved by the game, compiling an option pattern for each participant.

*Feasibility and acceptability*. For measuring feasibility, we will use the short version of the Game User Experience Satisfaction scale (GUESS-18 [45];). The scale has 18 items on a 7-point Likert scale (“strongly disagree” to “strongly agree”). It has 9 subscales (with two items each) covering aspects of gaming: usability/playability, narratives, play engrossment, enjoyment, creative freedom, audio aesthetics, personal gratification, social connectivity, and visual aesthetics. We will exclude the subscale “social connectivity” as the game is not a multiplayer game. Scores of different subscales can be added for an overall score. First validity measures show excellent convergent validity, with all subscales above 0.722. Reliability is *α* = .785 for the overall scale. In addition to the GUESS-18, we will analyse the time that was spent on the game and perform sensitivity analyses for drop-outs. The measure will be translated into German by the same procedure as described before.

*Gender*. Gender (in contrast to sex) will be assessed with the Inventar zur Erfassung des Geschlechtsrollen-Selbstkonzepts im Jugendalter (GRI-JUG [46];). This instrument assesses gender identity on four subscales: positive and negative feminine (communal; e.g. “emotional”, “vengeful”) and masculine (agentic; “companionable”, “lazy”) attributes. Each of the subscales consists of 5 items, yielding a total of 20 items. Subjects are asked to rate how much the attributes relate to themselves on a 5-point Likert scale (“does not apply at all” to “applies (nearly) always”). Internal consistencies of the scales are α = .81 (Mas+), *α* = .80 (Mas−), *α* = .88 (Fem+), and *α* = .74 (Fem−). Official English translation of the items exists.

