#### Secondary analyses

*Emotion regulation and emotional competence*. For the two questionnaires about emotion regulation and emotional competence, comparisons between groups will be performed for the pre-test and for the change between pre- and post-test (items change in the Likert scale is set to + 1 or − 1 if the Likert scale improves or worsens, by one point, respectively, and so forth). For both analyses, a Wilcoxon test will be performed.

*Sex differences within the experimental group*. Adaptive iER strategies will be dichotomised into positive engagement vs acceptance and for each participant the more frequent strategy will be determined. Our outcome variable is the proportion of which sex uses positive engagement (or acceptance). A chi-square test will be calculated to compare the percentage between the sexes. Second, a logistic regression analysis will be performed to evaluate if gender stereotype scores have an influence on the more frequent strategy positive engagement or acceptance. Note that for this analysis only adolescents from the experimental group will be considered.

*Feasibility*. Data from the feasibility questionnaire will be analysed using descriptive statistics. Open questions will be analysed qualitatively following thematic analysis [48].

For the secondary and exploratory analyses, the significance level for all tests is set to 0.05, *p*-values are interpreted in a descriptive manner. The statistical software programs R and SPSS will be used [49, 50].

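### The sex-difference analysis reduces up to 10 in-game choices to a majority class, which leaves equal counts without a class and discards strength of preference

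*Protocol article*

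**What the plan says.** Under Secondary outcomes (Sex differences), the article says that "the player undergoes 10 different scenarios, where they interact with NPCs by choosing one of up to four dialogue options". Each scenario offers two to four adaptive options, and both positive engagement and acceptance are always among them. On what is stored: "Each picked option will be saved by the game, compiling an option pattern for each participant".

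Under Secondary analyses (Sex differences within the experimental group), the rule is: "Adaptive iER strategies will be dichotomised into positive engagement vs acceptance and for each participant the more frequent strategy will be determined". Then: "A chi-square test will be calculated to compare the percentage between the sexes". A logistic regression of the same two-class outcome on gender stereotype scores follows. Only the experimental arm is used. Secondary tests are run at 0.05 and their p-values are read descriptively.

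Sex differences are one of three research questions. The hypothesis is directional: girls towards positive engagement, boys towards acceptance. The article gives no tie rule and does not say which saved pick counts if a scenario yields more than one. It gives no sample size or power for this comparison.

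**The concern.** An even number of choices between two classes produces ties, and a majority rule does not define the outcome for a tied player. Both planned analyses inherit that gap. Ties could be dropped, counted as positive engagement or counted as acceptance. These options compare different proportions, and a choice made after seeing the data could decide whether the result is significant.

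Even with a tie rule in place, the majority class throws away how strong each player's preference is. In one arm of a trial sized for a different question, that loss of information matters.

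**Working it through.** **The plan's own figure.** No number is given for the sex analysis, so the primary sample size sets the scale. For 30% versus 10%, two-sided 0.05, 80% power, no continuity correction:

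n = [1.96 × √(2 × 0.20 × 0.80) + 0.842 × √(0.30 × 0.70 + 0.10 × 0.90)]² / 0.20² = 61.6, so 62 per group (power 80.3%). With 30% drop-out, 62 / 0.7 gives 89 per group, 178 in total; the article states 180. The figure reproduces. The experimental arm is therefore about 90 randomised and about 62 completers.

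**Tie probability.** For 10 independent adaptive picks, each positive engagement with probability p, P(5:5) = C(10,5) × p⁵ × (1 − p)⁵. At p = 0.50 this is 252/1024. The documents give no choice probabilities, so p is an assumption.

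| p | P(5:5) | Tied among 62 | Tied among 90 |
|---|---|---|---|
| 0.50 | 24.6% | 15 | 22 |
| 0.60 | 20.1% | 12 | 18 |
| 0.70 | 10.3% | 6 | 9 |

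Two departures from this case:
- Players differ in preference. With a beta-binomial spread, correlation 0.05 to 0.30 and mean 0.50, the tie rate is about 20% down to 10%.
- Some picks are maladaptive and drop out. If each pick is adaptive with probability 0.5 to 0.9, the tie rate at p = 0.50 is about 14-18%. For a player left with exactly 8 or 6 adaptive picks it is 27.3% or 31.3%; with an odd number it is zero.

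A range of about 10-25% covers most of these cases. A quarter is the no-preference case, not a strict ceiling.

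**Effect of the tie rule.** Assume 31 girls at p = 0.60 and 31 boys at p = 0.50, with 10 adaptive picks each. The chances of more than five, exactly five and fewer than five positive-engagement picks are 0.633, 0.201 and 0.166 for girls, and 0.377, 0.246 and 0.377 for boys.

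| Tie rule | Girls | Boys | Power (normal approximation) |
|---|---|---|---|
| Dropped | 0.633/0.799 = 79% | 0.377/0.754 = 50% | 57% |
| Counted as positive engagement | 83% | 62% | 46% |
| Counted as acceptance | 63% | 38% | 52% |

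Comparing the mean count instead gives 71%.

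**Simulation of the same setting**, with players varying around their sex mean:

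| Within-player correlation | Majority chi-square, ties dropped | t-test on each player's share |
|---|---|---|
| 0 | 59% | 71% |
| 0.05 | 44% | 53% |
| 0.10 | 35% | 44% |

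Repeat runs agree to within one or two points. Type I error is about 5% for both methods. The three tie rules fail to agree on significance at 0.05 in about 31%, 27% and 22-24% of trials at correlation 0, 0.05 and 0.10. When only 60-80% of the 10 picks are adaptive and both methods use the same picks, the share comparison stays ahead; at 80% adaptive and correlation 0 it has about 59% power against 47%.

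**The case against.** **A tie convention is a detail for the analysis plan, which is not shown.** This stands in part, since an unseen plan may contain one. But the article itself fixes the majority class as the endpoint, and the loss of preference strength remains under any tie rule.

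**The test is valid and the outcome minor.** Type I error is indeed about 5%, the framework is exploratory and the p-values are descriptive. This limits the priority but does not make the rule a good one.

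**The numbers rest on assumptions.** They do: 60% versus 50%, equal numbers of boys and girls, and 62 players. Choices are recorded during play, so players who skip the post-test may still contribute.

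**Restricting to first picks could lose the gain.** This also stands. Compare the share among adaptive first picks with the majority rule on 10 resolved picks, at correlation 0/0.05/0.10. If 80% of first picks are adaptive, power is 58/49/39% against 58/44/34%. If only 60% are, it is 45/38/33% against 58/43/35%. First picks should therefore not be the main analysis.

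**A stronger reading that the documents do not support.** The Feedback section says that "the player cannot proceed and finish the game when using the wrong (i.e. maladaptive) strategies". A reader might infer that feedback steers the choices being compared, or that forced repeat picks enter the tally. The feedback described separates adaptive from maladaptive options; nothing says it favours positive engagement over acceptance. No forced retry of the same scenario is described. The hypothesis itself concerns choices made within the game.

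**Conclusion.** The point holds for the classification rule. As written, it gives no class to players with equal counts, about 10-25% of them under plausible assumptions and 24.6% for 10 independent, evenly split adaptive picks. It also discards strength of preference. In the assumed setting this costs about 9 to 12 percentage points of power compared with using each player's share of the same picks, and the unstated tie rule changes significance in about a quarter to a third of trials. Ties and disagreements are fewer when some picks are maladaptive.

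The point does not show that the test is biased, or that the game's feedback distorts the sex contrast. Because the analysis is secondary with descriptive p-values, it is a worthwhile improvement of modest priority.

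**What to change.** Replace the majority rule, in both the sex comparison and the gender-score regression, with each player's count or share of positive-engagement picks among adaptive picks. A logistic regression with sex and scenario as factors, and participant handled by a random effect or GEE, would do this. State that one adaptive pick per scenario is counted. Report the difference between the sexes with a 95% CI. An analysis limited to first picks can be a sensitivity analysis. If the majority rule is kept, fix the handling of equal counts before the data are seen.

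The cost is a change of wording and a slightly more complex model. No new data are needed, because the game already saves every pick.

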### Objectives {7}

In this RCT, we will assess the impact of the web-based serious game on iER skills in early adolescents. The primary objective of this study is to compare the improvement in pre- and post-intervention knowledge about iER strategies between a group that plays the intervention/serious game and a control group that plays a game without psychoeducational content. The secondary objectives are to examine sex differences in the use of specific strategies and to evaluate feasibility and acceptability of the intervention. We will examine the effects on outcomes of the following potential confounding variables: gender, prior gaming experience, language, and pER.

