### Outcomes {12}

Our primary outcome in this study is the change of iER strategies participants can think of from pre (baseline)- to post-intervention, i.e. if the percentage of participants who improve their knowledge about possible iER strategies is higher in the experimental group compared to the control group. This is done via a vignette-task. The follow-up will be approximately 5 days after baseline measures.

In secondary analyses, we will test iER as a corroborating variable with a questionnaire. The questionnaire was not developed to measure change of iER skills over a short period of time (it asks for iER strategies use in the last 2 weeks) and is thus used as a complementary measure. As the game addresses general topics around emotions additionally to specific iER strategies, we will also examine the change in general emotional competence. Furthermore, effects of sex and gender on strategy choice and feasibility of the game will be examined.

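### The gender regression names only the gender-role scores; unless sex is also in the model, a sex difference can appear as a gender-role influence

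*Protocol article*

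**What the plan says.** The Outcomes section promises that "effects of sex and gender on strategy choice and feasibility of the game will be examined". The description of secondary outcomes treats the two as different constructs: "Gender (in contrast to sex) will be assessed with" a gender-role inventory, and "This instrument assesses gender identity on four subscales: positive and negative feminine", with masculine counterparts. The Hypotheses section expects girls to lean towards positive engagement and boys towards acceptance.

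Under Secondary analyses, each child's more frequent adaptive strategy (positive engagement or acceptance) is the outcome. Two analyses follow:

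- For sex: "A chi-square test will be calculated to compare the percentage between the sexes".
- For gender: "Second, a logistic regression analysis will be performed to evaluate if gender stereotype scores have an influence on the more frequent strategy".

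Both concern one arm: "Note that for this analysis only adolescents from the experimental group will be considered". The 0.05 level applies, with p-values read descriptively. Sex is asked at the start of the questionnaires, so it is available as a covariate.

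**The concern.** Sex and gender role are examined on the same outcome, in the same children, in two analyses that do not adjust for each other. If girls score higher on feminine attributes or boys on masculine ones, and sex affects strategy choice as hypothesised, the scores act partly as a proxy for sex. A regression on the scores alone then gives them non-zero coefficients even when gender role has no effect of its own.

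At stake is how a positive gender result is read. From the scores-only model, a reader could not tell whether gender role matters or whether the sex difference from the preceding test has been seen again. Labelling the p-values as descriptive does not cure this, because the coefficients themselves are shifted.

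**Working it through.** **1. How many children.** The document gives no sample size for this regression, so the primary calculation sets the scale. For 30% vs 10%, two-sided 0.05, 80% power:

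n = [1.960 × √(2 × 0.20 × 0.80) + 0.842 × √(0.30 × 0.70 + 0.10 × 0.90)]² / 0.20² = (1.109 + 0.461)² / 0.04 ≈ 61.6, so 62 per group, as stated. Allowing for 30% drop-out, 124 / 0.70 ≈ 177.1, so 178; the plan rounds to 180. The experimental arm therefore has 180 / 2 = 90 children randomised and about 90 × 0.70 = 63 completers. I use 62 and 90.

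**2. Assumptions, none of them from the document.** Half the children are girls. Preference for positive engagement is 70% in girls and 40% in boys (60% vs 40% as a milder case). There are four standard-normal scores, independent within sex; one is d SD higher in girls and one is d SD lower, and the other two do not differ. Given sex, the scores have no effect on strategy.

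**3. Size of the shift.** On the linear probability scale, the coefficient that a shifted score borrows from sex is (sex effect) × (d/4) / (1 + d²/2). With a sex effect of 0.70 − 0.40 = 0.30:

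- d = 0.3: 0.30 × 0.075 / 1.045 = 0.022
- d = 0.8: 0.30 × 0.200 / 1.320 = 0.045
- d = 1.2: 0.30 × 0.300 / 1.720 = 0.052

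So one SD on such a score appears to move the preference by about 2 to 5 percentage points when its true effect is zero.

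**4. How often it looks significant.** Logistic regression, joint likelihood-ratio test of the four scores at 0.05, 1,500 simulated trials per setting. Each cell shows the rate without sex / with sex in the model:

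| Sex gap d | n=62, 70% vs 40% | n=90, 70% vs 40% | n=62, 60% vs 40% | n=90, 60% vs 40% |
|---|---|---|---|---|
| 0 | 7.1% / 6.3% | 5.7% / 5.5% | 5.9% / 6.4% | 6.1% / 6.2% |
| 0.3 | 8.1% / 6.7% | 6.5% / 5.5% | 7.4% / 7.1% | 5.4% / 5.5% |
| 0.5 | 9.5% / 6.4% | 11.1% / 6.9% | 7.7% / 8.1% | 7.7% / 6.2% |
| 0.8 | 14.1% / 6.0% | 17.3% / 6.1% | 9.9% / 7.3% | 10.7% / 7.0% |
| 1.2 | 21.5% / 7.1% | 29.9% / 6.8% | 13.1% / 7.1% | 15.2% / 5.7% |

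Simulation error is about √(0.06 × 0.94 / 1,500) = 0.6 percentage points at the low end and √(0.215 × 0.785 / 1,500) = 1.1 at 21.5%.

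**5. Reading the table.** With no sex gap on the scores, leaving out sex does no harm. With a gap, the false-signal rate rises with the gap, with the sex effect and, at the larger gaps, with the number of children. Adding sex brings the rate back near nominal; the small excess over 5% occurs with and without a gap.

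**6. Cost to the model.** At 70% vs 40%, about 62 × 0.45 ≈ 28 children fall in the rarer class. Four coefficients give 28 / 4 = 7 per coefficient, five (with sex) 28 / 5 = 5.6, and six (with language too) 28 / 6 = 4.7.

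**The case against.** The best defence is that the sentence states the purpose of a secondary model and is not a full specification. It does not say how the four subscales enter, nor that sex is left out, and a condensed article may leave such detail to a fuller document. That stands in part: a reader might infer that the plan excludes sex, and the document does not say so. Against it, the primary logistic regression in the same article lists its independent variables, covariates included. Here the text names the scores alone, and nothing else in the article describes a joint model of sex and gender.

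A second defence is that the plan never promises mutually adjusted effects; two separate associations would satisfy the wording in the Outcomes section. That is fair as a literal reading. But the plan measures gender as distinct from sex, speaks of *influence*, and lists gender among potential confounders ("We will examine the effects on outcomes of the following potential confounding variables: gender, prior gaming experience, language, and pER"). An unadjusted score coefficient serves those purposes poorly.

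Third, the sex gap on the scores is assumed. The document gives subscale names, example items and internal consistencies, but no scores by sex. This stands, and it makes the problem conditional.

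Fourth, the trial is described as exploratory, and this is a non-randomised comparison within one arm with descriptive p-values. This also stands and limits the weight of the point.

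**Conclusion.** The point holds in a limited form. As written, the gender regression names only the gender-role scores, so a sex difference can appear as a gender-role influence. With 62 children and assumed preferences of 70% vs 40%, the scores are jointly significant in about 8% to 22% of trials for assumed sex gaps of 0.3 to 1.2 SD, against about 6% to 7% with sex in the model. At 60% vs 40% the range is about 7% to 13%, against 7% to 8%.

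Two stronger readings are not supported. A reader might infer that a sex difference *will* be reported as a gender effect. Even in the worst setting at 62 children, 100% − 21.5% = 78.5% of trials give no such signal, and with no sex gap there is no confounding. A reader might also infer that sex and gender role cannot be separated in this trial. That describes the model as worded, not the design, because sex and all four scores are collected.

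The analysis is secondary and descriptive. The primary comparison and the sample size are untouched.

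**What to change.** Under Secondary analyses, state that the logistic regression of preferred strategy includes sex as a covariate together with the gender-role scores, and that the score coefficients are interpreted from this model. The chi-square test by sex can stay as it is.

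No new data are needed, and the Trial status section places the trial before recruitment. The cost is one more coefficient and somewhat wider intervals in about 63 to 90 children.

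Adjusting for language is optional. The objectives name it as a potential confounder, but its effect on this analysis has not been quantified, and a sixth coefficient would leave fewer than five children in the rarer class per coefficient at the smaller sample size.

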### Interim analyses {21b}

We do not expect the trial to result in any harmful side effects, and due to online administration, the process will not be monitored. Yet, after an internal pilot phase of 40 participants, we will look at drop-out rates and—if patterns are found during questionnaire completion—possibly change the settings of the online questionnaires to allow participants to skip questions and increase adherence.

### Methods for additional analyses (e.g. subgroup analyses) {20b}

The additional analyses such as subgroup analyses are already covered by the secondary outcome analyses.

### Methods in analysis to handle protocol non-adherence and any statistical methods to handle missing data {20c}

Missing values will be avoided by not allowing participants to skip questions. Drop-outs will be considered in sensitivity analyses based on the intention-to-treat principle, which means that all participants are considered in the analyses regardless if they completed all questionnaires or not. No data imputation for missing data will be performed.

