## Statistical methods

### Statistical methods for primary and secondary outcomes {20a}

#### Randomisation

To evaluate the randomisation process, baseline variables will be compared between experimental group and control group, first based on the intention-to-treat principle, which means that all participants are considered in the analyses regardless if they completed all questionnaires or not. Second, the baseline comparison will be repeated for the main analysis sample, which comprises all participants with completed questionnaires.

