#### Primary analysis—interpersonal emotion regulation skills

First, descriptive statistics will be generated for each observation time (pre- and post) and for each group: for continuous variables, mean and standard deviation (or median and interquartile range in case of a skewed distribution, respectively) and for categorical variables absolute and relative frequencies will be computed.

Answers of the vignette task will first be qualitatively assessed to exclude maladaptive as well as nonsensical strategies and merge answers that can be defined to be the same strategy. To analyse the main question, the change in the absolute number of positive strategies between pre- and post-test as well as the percentage of adolescents with a positive change in iER skills will be considered. A chi-square test (main analysis) will be calculated to compare the percentage between the two groups. Then, a logistic regression analysis will be performed for the dependent variable “positive change yes/no” to investigate the influence of the independent variables “time between last time of playtime and post-test”, “language”, “total playtime”, and “group”. To compare the change in absolute numbers, a non-parametric Wilcoxon rank-sum test will be performed (secondary analysis). The significance level will be set to 0.05.

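### The intention-to-treat sensitivity analysis in {20c} cannot include participants without a post-test, because the endpoint requires one and imputation is ruled out

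*Protocol article*

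**What the plan says.** - **Endpoint.** Outcomes {12} defines the primary outcome as "the change of iER strategies participants can think of from pre (baseline)- to post-intervention", expressed as the percentage of participants who improve.
- **Test.** Under the primary analysis in {20a}: "A chi-square test (main analysis) will be calculated to compare the percentage between the two groups". The same section adds a logistic regression on the yes/no change and a Wilcoxon rank-sum test on the change in number of strategies.
- **Main sample.** The Randomisation paragraph of {20a} refers to "the main analysis sample, which comprises all participants with completed questionnaires".
- **Drop-outs.** Section {20c}: "Drop-outs will be considered in sensitivity analyses based on the intention-to-treat principle", explained as meaning that "all participants are considered in the analyses regardless if they completed all questionnaires or not". The next sentence is "No data imputation for missing data will be performed".
- **Expected loss.** Sample size {14} allows for about 30% drop-out, giving 180 in total.
- **Timing.** Sequence generation {16a} places randomisation at the end of the pre-test, so a randomised drop-out has a baseline but no post-test.

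**The concern.** The two rules in {20c} cannot both be followed for a participant who never returns the post-test. Such a participant has no yes/no change, so including them in the chi-square test means assigning a value, which the no-imputation sentence forbids on its usual reading. Forced answers in the online questionnaire prevent skipped items, not an unreturned post-test.

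At stake is the plan's main safeguard for a comparison restricted to completers. The arms ask for different things: the experimental game takes about 3 h to complete, while controls are told to play the puzzle game as much as they want. Drop-out could therefore differ between arms in rate or in kind. Enlarging the sample to 180 restores precision but does nothing about selective loss.

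**Working it through.** **1. The plan's own figures.** Inputs from {14}: 30% versus 10% improving (the section's wording is loose; read here as proportions of participants), significance level 0.05 taken as two-sided, 80% power. The standard two-proportion formula without continuity correction gives 62 per group, with power 0.803. Inflation: 124 / (1 − 0.30) = 177.1, rounded up to 178, consistent with the stated 180. These figures reproduce.

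**2. How many have no endpoint.** 180 × 0.30 = 54 without a post-test; 180 − 54 = 126 with one, or 63 per arm if loss is equal.

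**3. Can the named tests use the 54?**

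| Planned analysis | Needs post-test? |
|---|---|
| Chi-square on percentage improved | Yes |
| Logistic regression on change yes/no | Yes |
| Wilcoxon rank-sum on change in number | Yes |

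No rule classifies a participant without a post-test, and no model using baseline-only records is named. The sensitivity set can exceed the completer set only by people who did the vignettes twice but did not finish every questionnaire.

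**4. Does the handling matter?** The arm-specific drop-out rates are assumptions; the protocol gives none. With 90 randomised per arm and completer rates near the planned ones (chi-square without continuity correction):

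| Drop-out, exp. / control | Completers | Drop-outs counted as not improved |
|---|---|---|
| 30% / 30% | 19/63 v 6/63, p = 0.004 | 19/90 v 6/90, p = 0.005 |
| 40% / 20% | 16/54 v 7/72, p = 0.004 | 16/90 v 7/90, p = 0.044 |
| 45% / 15% | 15/50 v 8/76, p = 0.006 | 15/90 v 8/90, p = 0.118 |

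Worst case at 30% / 30% (experimental drop-outs all not improved, control drop-outs all improved): 19/90 = 21.1% versus (6 + 27)/90 = 36.7%, which reverses the direction.

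**5. Selective loss with no true effect.** Assume that 40% of non-improvers and 10% of improvers leave the experimental arm, and that control drop-out is 30% and unrelated to outcome. With true rate p in both arms, the experimental completer rate is 0.9p / [0.9p + 0.6(1 − p)]. Counting drop-outs as not improved gives 0.9p versus 0.7p, with 90 per arm.

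| p | Completers, exp. v control | Rejection rate | Counted as not improved | Rejection rate |
|---|---|---|---|---|
| 0.10 (plan's control rate) | 14.3% v 10% | about 11% | 9% v 7% | about 8% |
| 0.20 | 27.3% v 20% | about 15–16% | 18% v 14% | about 11% |
| 0.40 | 50% v 40% | about 20–21% | 36% v 28% | about 21% |

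The nominal rate is 5%. The single rule lowers the error in the first two rows, leaves it unchanged in the third, and removes it in none.

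**6. Power cost of the single rule.** Under the plan's rates and equal 30% drop-out: 0.30 × 0.70 = 21% and 0.10 × 0.70 = 7%. With 90 per arm, power is 0.777 by the normal approximation and 0.793 by exact enumeration. Completers alone, 63 per arm, give 0.809 by the normal approximation.

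**The case against.** **The sensitivity analysis does not simply duplicate the main one.** A reader might infer that it collapses to the completer analysis. The text does not support that: the main sample requires completed questionnaires and the sensitivity set does not, so someone with both vignettes and an unfinished later questionnaire could be added without imputation. This stands and limits the point to participants with no post-test vignette.

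**The plan is not blind to attrition.** It would also go too far to say that nothing in the plan examines who stayed. Baseline variables are to be compared between arms in all participants and again in the main sample ({20a}); the feasibility paragraph of {18a} mentions sensitivity analyses for drop-outs; and drop-out rates are reviewed after 40 participants ({21b}). These are partial checks on measured characteristics and on rates. They cannot show whether leaving was related to an outcome nobody observed.

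**Skipped items.** One might argue that a single skipped item elsewhere would remove a child from the primary analysis. That depends on {21b}, which says only that the team may "possibly change the settings of the online questionnaires to allow participants to skip questions and increase adherence", and on reading completion as answering every item rather than reaching the end. It is a reason to define the sample clearly, not a present fault.

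**An unseen analysis plan could settle it.** The choice of estimator can be left there, and a likelihood-based repeated-measures model of strategy counts could use baseline-only records without imputation. But no such model is named, and further detail cannot reconcile {20c} with the yes/no tests that {20a} does name.

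**The trial is exploratory, and the completer analysis is openly declared and can be run.** This stands, and it lowers the severity.

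**Conclusion.** The contradiction is in the stated text and holds for participants without a post-test: about 54 of 180 at the protocol's own 30% drop-out. As written, the intention-to-treat sensitivity analysis cannot include them, and the remaining checks do not reach drop-out related to the unseen outcome. The count of 54 rests only on the protocol's figures. The p-value shifts and error rates rest on assumed drop-out patterns; they show that handling can change the conclusion, not that it will. The sample size is not wrong, and the completer analysis is not shown to be biased. This should be fixed before outcome data are seen by arm.

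**What to change.** In {20a} and {20c}:

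1. Define the main analysis sample as all randomised adolescents with the vignette task at both time points, analysed as allocated, irrespective of other questionnaires.
2. Limit the no-imputation sentence to the main analysis.
3. Specify an all-randomised sensitivity analysis that can be run, for example a missing post-test counted as no positive change. Pair it with a best/worst-case or tipping-point analysis that varies the assumed improvement rate among drop-outs by arm, since the single rule does not by itself remove bias from selective drop-out.
4. Report drop-out by arm.

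Multiple imputation with a fixed covariate list is optional. The cost is a few sentences and some extra analysis, with no new data. Under the plan's rates and equal 30% drop-out, the analysis counting drop-outs as not improved has about 78–79% power, against about 81% in completers.
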